### Outcome measures

The primary outcome measure is frequency of FI among patients 6 months after start of the intervention, as measured by The interRAI Long-Term Care Facilities Assessment System (interRAI LTCF) [36], section H3: Bowel continence with the categories 0 to 5 (0 = continent, 1 = continent with stoma, 2 = seldom incontinent, 3 = occasionally incontinent, 4 = often incontinent, 5 = incontinent). The interRAI LTCF is an internationally validated questionnaire regarding long-term care patients’ health conditions. In order to get some additional information about the severity of FI and urgency, a Norwegian version of the St. Mark’s anal incontinence score [37] will be used. The St. Marks grading system is based on the type and frequency of anal incontinence (gas, fluid, or solid) and the impact on daily life, the need to wear a pad/diaper and/or anal plug, the use of constipating medication and the presence of urgency. It gives a total score from 0 (complete continence) to 24 (complete incontinence).

The study has the following secondary outcome measures:*Remission of FI* among patients identified with FI at baseline, or *incidence* of new cases of FI among patients identified as continent at baseline, measured by interRAI LTCF section H3 and the St Marks score.*Change in FI related concerns* measured by interRAI LTCF: section E: Mood and behavior, section F: Psycho-social wellbeing, section H1: Urinary continence, section J: State of health - Constipation and diarrhea, section L: Skin condition, and section M: Participation in activities.*Change in knowledge* among RNs/ASEs measured by multiple choice tests developed by the researchers according to established guidelines [38].*Change in documented care for FI by health personnel as registered in the EPR*: RNs/ASEs will extract data from the EPR. The instrument N-Catch [39] will be used for this purpose. N-Catch is an audit instrument for nursing reports in the EPR. N-Catch is translated into Norwegian and developed based on the validated D-Catch [40] and Cat-ch-ing [41]. Change in care will also be measured by the Fecal Incontinence in Nursing Home Patients questionnaire [6] where RNs/ASEs are offered a list of interventions for FI, urinary incontinence, diarrhea and constipation and asked to identify what is done for each individual patient.*Change in cost* of FI management measured by mapping the use of products (diapers, pads, plugs) and bowel medications measured by interRAI LTCF section H: Continence - remedies, section N: Medications, and the Fecal Incontinence in Nursing Home Patients questionnaire.*Correlates of FI* among NH patients measured by interRAI LTCF: section C: Cognitive functioning, section D: Communication and vision, section G: Functionality and mobility, section I: Medical diagnoses, section J: Health condition, section K: Mouth- and nutrition status, section N: Medications, and section O: Treatment, examinations/procedures.

Process evaluation will include attendance at the pedagogical program and use of the FI-guideline. Evaluation will be conducted by using checklists administered by the researchers: proportion RNs/ASEs within eligibility criteria participating in the workshop, proportion of staff participating in the educational outreach meetings, proportion of patients assessed by the FI-guideline, and proportion of patient assessments resulting in an individualized care plan in the EPR.

### Background variables

Organizational characteristics of the NHs and background information on patients’ sex, medical status and length of stay in the NH will be obtained. Background variables for the RNs and ASEs are age, sex, educational level, years since registered/authorized and length of employment at the present site.

### Sample size

Sample size calculations are based on the primary outcome: frequency of FI among patients. The power calculations have taken into account the results from the pilot study. The pilot study identified the primary outcome variable to be skewed to the right, and methodological consideration resulted in a dichotomization of the primary outcome variable with a cut off between 2 (continent, continent with a stoma and seldom incontinent) and 3 (occasionally incontinent, often incontinent and incontinent). Based on results from the pilot study, we hypothesized that a reasonable and clinically important effect size in the intervention group compared to the control group would be 15% between the two groups in proportions with FI (score of 3 to 5). As the design is a cluster randomized trial, we need to adjust for clustering. The intracluster correlation coefficient (ICC) is estimated to be 0.04. The estimate is based on published patterns in ICCs [23,42-44], and results from the pilot study where the ICC was calculated to be 0.038. In addition, we had access to the FI variable with the categories 0 to 4 from an epidemiological study of 980 NH patients in Trondheim municipality [6] with an ICC calculated as 0.028. Based on the assumptions of the mixed logistic binominal model, 5% level of significance, test strength of 80%, an average cluster size of 15 patients, and an ICC of 0.04, a study population of 103 patients in each arm of the C-RCT is needed. The number of individuals in each cluster is set because each unit has a fixed number of beds. Assuming a 15% dropout, the sample needed is 120 patients in each arm. This means a total of 240 patients and about 20 NH units (Figure 1).

In addition, the number of patients records needed for data extractions, was calculated. N-Catch measures the quality of the content in the EPR on a scale from 0 to 32 where 0 is low quality and 32 is high quality [39-41]. Based on the assumption of a paired *t*-test, a 5% level of significance, test strength of 80%, an effect size of 3 points and an ICC of 0,04, records from 6 patients per cluster is needed for a total of 146 records (Figure 1).

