## Background

Fecal incontinence (FI) is defined by the International Consultation on Incontinence as ‘the involuntary loss of liquid or solid stool that is a social or hygienic problem’ [1]. FI has a higher prevalence in the elderly population than in younger people, which cannot be explained by comorbidity or the anatomical and psychological changes of aging alone [2]. In the nursing home (NH) population, previous studies suggest a prevalence of FI between 10 and 69% [3-5], but it is most often reported to be between 40 and 55% [1,5,6]. The varying prevalence may be due to the lack of a consistent definition of FI, although differences in the quality of continence care in the NHs might also be an explanation [6,7].

FI leads to a high direct and indirect economic burden to the healthcare system, and is an important cause of institutionalization of older patients [1,2,7]. In addition, FI is associated with shame, social isolation and reduced quality of life [1,8,9]. FI among older patients has a more complex etiology compared to the younger population [2,6], and the importance of identifying treatable causes of FI in frail older people, rather than just managing symptoms passively, is strongly emphasized [1]. The level of awareness among health personnel regarding appropriate assessment and treatment options for FI seems limited [1,10-12]. Further, there are indications that both older patients themselves and health personnel consider FI to be a normal part of aging for which nothing can be done [9,11]. It is recommended that an assessment of FI should be implemented as part of an evaluation of older patients [1,2,13].

There is a substantial evidence base to guide choice of implementation activities targeting healthcare professionals in general [14-17]. However, relatively little of the implementation research has focused on the care of older people or involved care processes or care personnel [18]. Even though the evidence is not fully conclusive, implementation research suggests that the most effective method for changing the behavior of health personnel in long-term care settings involves multifaceted educational efforts such as written materials or toolkits combined with individual educational visits, small group training or feedback [14,17,19].

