### Recruitment

Approval will be obtained from the director for health and social affairs in the municipality. The first and last authors will participate in a meeting where all managers for the NHs in the municipality will be gathered. The project will be presented and NHs invited to participate. NHs accepting the invitation will be eligible for selection. NH units will be enrolled until the target patient sample size is reached.

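### The 103 patients per arm cannot be reproduced because the control-arm proportion is not given, and 240 patients, 15 per unit and about 20 units do not fit together

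*Protocol article*

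**What the plan says.** All references are to the protocol article.

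- **Sample size, inputs.** The primary outcome is dichotomized between scores 2 and 3. The target effect "would be 15% between the two groups in proportions with FI (score of 3 to 5"). The other inputs are "5% level of significance, test strength of 80%, an average cluster size of 15 patients" and an ICC of 0.04. Sidedness is not stated, and neither is the proportion expected in either arm.
- **Sample size, result.** From these inputs the section states "an ICC of 0.04, a study population of 103 patients in each arm of the C-RCT is needed". It allows 15% dropout, reaches 120 per arm, and concludes: "This means a total of 240 patients and about 20 NH units".
- **Background.** This holds the only prevalence figures. It says "previous studies suggest a prevalence of FI between 10 and 69"%, and that "it is most often reported to be between 40 and 55"%.
- **Setting.** Units most commonly have 15 beds. The Sample size section adds that the beds fix the number of patients per unit.
- **Recruitment.** "NH units will be enrolled until the target patient sample size is reached". The Abstract gives the number of units to be recruited as twenty.

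**The concern.** A difference between two proportions has no sample size until one of the proportions is fixed, because the variance depends on it. The section prints every other input and then an exact answer. A reader who fills the gap with the prevalence in the article's own Background gets more than twice 103.

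The 80% power claim governs how a null result is read. If power for 15 points were nearer 45%, a non-significant result would say little about whether the program works.

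The mismatch between patients and units matters because enrolment is tied to the patient count, while the number of randomized units and homes carries much of the information in a cluster trial.

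**Working it through.** **Inputs.** Difference 0.15, read as percentage points; α = 0.05, two-sided by assumption; power 0.80; cluster size m = 15; ICC = 0.04 (all from Sample size). Control proportion p₁: not stated. The 40 to 55% from the Background is used as an assumption, with lower values alongside. Reading 15% as points is the favourable choice: a 15% relative reduction from 40 to 55% would need 1,016 to 576 per arm before clustering.

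**Formulas.**
- Design effect: DE = 1 + (m − 1) × ICC = 1 + 14 × 0.04 = 1.56.
- Per arm before clustering: n = [1.960 × √(2p̄(1 − p̄)) + 0.842 × √(p₁(1 − p₁) + p₂(1 − p₂))]² / (p₁ − p₂)², where p̄ is the mean of p₁ and p₂. Multiply by DE for clustering.
- Power at N per arm: the same expression solved for power, with effective size N / DE.

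**Trying to reproduce 103.** 103 / 1.56 = 66 effective patients per arm. Solving for the control proportion at which 15 points needs 66 gives p₁ ≈ 18%, p₂ ≈ 3%. If the design effect is omitted, 103 per arm corresponds to p₁ ≈ 26%, p₂ ≈ 11%. A one-sided 5% test with the design effect gives about 21.5% falling to 6.5%.

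**Worked case, 40% falling to 25%.** p̄ = 0.325; √(2 × 0.325 × 0.675) = 0.662; √(0.24 + 0.1875) = 0.654. The sum is 1.960 × 0.662 + 0.842 × 0.654 = 1.849. Then 1.849² / 0.0225 ≈ 152 per arm, and 152 × 1.56 ≈ 237.

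| Control, falling by 15 points | n per arm, no clustering | n per arm × 1.56 | Power, 103 per arm | Power, 120 per arm |
|---|---|---|---|---|
| 18% | 65 | about 101 | 81% | 87% |
| 25% | 100 | about 156 | 62% | 69% |
| 30% | 121 | about 189 | 54% | 61% |
| 40% | 152 | 237 | 45% | 51% |
| 50% | 170 | 265 | 41% | 47% |
| 55% | 173 | 270 | 41% | 46% |

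An unpooled variance moves the 103-per-arm figures up by about one point, so for 40 to 55% the range is 41 to 46%.

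**Checks on the 40 to 55% result.**
- With no design effect at all, 103 per arm gives 58 to 63% power. The planned adjustment for baseline cluster prevalence acts on between-cluster variation, so removing the whole clustering penalty would still not reach 80%.
- A one-sided 5% test needs 120 to 136 per arm before clustering and 188 to 213 after.

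**Detectable difference at 80% power, control 40 to 55%, DE 1.56.** About 22 to 24 points with 103 per arm; about 20.5 to 22 points with 120 per arm.

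**Totals.** 240 / 15 = 16 units. 20 × 15 = 300 patients. 240 / 20 = 12 per unit. Any two of the three figures exclude the third. With two units per home (Randomization and allocation), 16 units would be 8 homes and 20 units would be 10.

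**The case against.** The strongest reply is that the 40 to 55% describes a different quantity. It is prevalence of fecal incontinence across studies that, as the Background says, lack a consistent definition, and the range cited there runs from 10 to 69%. The trial counts seldom incontinent as not incontinent, and the pilot found the score right-skewed, so the control proportion may be lower. The calculation drew on an unpublished pilot, and the full protocol may give the missing figure. All of this stands. A reader might infer that the design plainly lacks 80% power, or that 103 is impossible. The documents do not support either: about 18% falling to 3% yields 103. Nor do they show that clustering was left out. The match at about 26% is only a coincidence of numbers, and the section says it adjusts for clustering.

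On the totals, the text says about 20 units, and 15 beds is only the most common size. Twelve eligible patients per unit would give 240 from 20 units exactly. A reader might infer that recruitment will end at 16 units, but that requires about 15 patients from every unit. Nor is the mismatch a further loss of power. With 12 per unit the design effect is 1 + 11 × 0.04 = 1.44, and power at 120 per arm rises slightly, to 49 to 54% at 40 to 55%.

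The dropout step is no error. 103 / 0.85 = 121.2 and 103 × 1.15 = 118.5, so 120 is rounding. Because the primary analysis is repeated cross-sectional, loss of baseline patients also need not reduce the six-month sample one for one.

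The condensed format does not dispose of the point. The article prints a calculation with all inputs but one, and totals that disagree with each other.

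**Conclusion.** The point holds in conditional form. The stated 103 per arm cannot be derived from the stated inputs, and the value that would produce it with the clustering adjustment (about 18% falling to 3%) means near-elimination of the outcome. The shortfall depends on the unstated control proportion. Power at 103 evaluable per arm is about 41 to 46% if that proportion is 40 to 55%, about 54% at 30%, about 62% at 25%, and 80% only near 18%. These figures assume a two-sided test, an absolute 15-point difference and a design effect of 1.56.

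The inconsistency among 240 patients, 15 per unit and about 20 units needs no assumption. Its practical consequence is a possibility and not a certainty: enrolment tied to the patient target could stop short of the twenty units named in the Abstract.

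**What to change.** 1. In Sample size, state the pilot-based control and intervention proportions for score 3 to 5, and whether the 5% test is two-sided.
2. Restate the power or detectable difference that the planned sample delivers with the design effect, and say whether it refers to 103 evaluable or 120 enrolled per arm. If the control proportion is 40 to 55%, the statement would be about 41 to 46% power for 15 points, or 22 to 24 points at 80% power, with 103 per arm. With 120 per arm it would be about 46 to 51% power, or 20.5 to 22 points.
3. Reconcile the average cluster size, the number of units and the total. If about 12 eligible patients per unit are expected, say so and use 12 in the design effect.
4. In Recruitment, define the enrolment target as the 20 units already planned instead of a patient count.

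The cost is one rewritten paragraph, one changed sentence and possibly a less favourable stated power. No units are added beyond the 20 planned. If every unit did supply 15 patients, the total would be 300 instead of 240.

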**Methods/design:**

The study is a two-armed, parallel cluster-randomized controlled trial. Primary outcome is the frequency of fecal incontinence among patients. Sample size calculations resulted in a need for a total sample of 240 patients. Twenty nursing home units in one city in Norway will be recruited and allocated to intervention or control by an independent statistician using computer-generated tables. The intervention is a multifaceted educational program. Units in the control arm will provide care as usual. The intervention period is 3 months. Data will be collected at baseline, 3, and 6 months. Data will be analyzed using mixed effect models with the cluster treated as a random effect.

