### Randomization and allocation

One unit will be defined as one cluster. Two clusters per NH will be recruited. Allocation stages are as follows:NHs will be identified and recruited;Units will be identified and recruited;Patients will be identified;Baseline data collection will take place for units and patients;Allocation will be done by an independent statistician to intervention or control; andRNs/ASEs will be identified and recruited to the intervention (Figure 1).

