### Data collection methods

Data are collected at baseline (t_0_), after 3 months (t_1_ = end of intervention), and after 6 months (t_2=_primary time of assessment). A research assistant will, together with the first author, give information and training on completion of the questionnaires and data extraction from EPR at baseline. RNs/ASEs will then be responsible for filling in the questionnaires about the patients’ health condition (proxy) and extracting the data from the EPR. Organized alphabetically by last name on a list, the EPRs of the first six patients per cluster will be extracted. Time scheduled for the information meetings is 2 to 3 hours per NH. The ward manager will fill in a form on organizational characteristics. When completed, the first author and research assistant will collect the data forms. At both t_1_ and t_2_ the research assistant will deliver, give necessary additional information and collect the completed forms. NHs will be offered economic compensation for the data collection.

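### Six records per unit in about 20 units gives 120 records for the N-Catch audit, not the 146 that the sample size section says are needed

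*Protocol article*

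**What the plan says.** The Sample size section of the protocol article has a separate calculation for the record audit, and it concludes that "records from 6 patients per cluster is needed for a total of 146 records". Its basis is given as "Based on the assumption of a paired *t*-test, a 5% level of significance, test strength of 80" per cent, together with a difference of 3 points on the 0 to 32 N-Catch scale and an intracluster correlation of 0.04. No standard deviation is given, and no attrition allowance is mentioned for records.

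The number of clusters is stated in two places. The abstract says "Twenty nursing home units in one city in Norway will be recruited", and the patient calculation ends with "This means a total of 240 patients and about 20 NH units". Under Randomization and allocation, "One unit will be defined as one cluster", two units are taken per nursing home, and all units of a home go to the same arm. Under Recruitment, "NH units will be enrolled until the target patient sample size is reached", so enrolment is tied to patients and not to records.

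Under Data collection methods the patients are listed alphabetically by last name, and "the EPRs of the first six patients per cluster will be extracted". The unit's own nurses and social educators do the extraction. The Discussion acknowledges that these staff take part in the intervention and are not blinded. Under Secondary outcomes, change in care is to be analysed as cross-sectional time series with mixed effects models.

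**The concern.** The records per cluster and the total are printed in one sentence, and they do not fit the number of clusters in the same section. The data collection rule then fixes the smaller yield in practice. If the plan is followed, the trial collects fewer records than it says it needs for this outcome, and the stated 80% power does not describe what will be analysed.

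Two further matters bear on the same outcome. The calculation names a test that does not appear in the analysis section, and it leaves open what the pairs are. The selection rule is also deterministic. Staff who have extracted the records once can work out which ones are likely to be audited later, and in the intervention arm those staff will in the meantime have been trained to document continence care in the record.

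**Working it through.** **Inputs (protocol article).** Records per cluster 6, total 146, intracluster correlation 0.04, difference 3 points, significance level 5%, power 80% (Sample size). Clusters 20 (abstract; about 20 in Sample size). Two units per home, homes allocated whole (Randomization and allocation). Assumption: a two-sided test, since sidedness is not stated.

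**1. Can 146 be reproduced as a product?**
- 6 x 20 = 120. Shortfall 146 - 120 = 26, and 26/146 = 18%.
- Clusters needed at 6 each: 146/6 = 24.3, so 24 (144 records) to 25 (150 records).
- Records per unit needed with 20 units: 146/20 = 7.3.

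**2. Do other readings give 146 with 20 units?**
- 15% attrition added: 120/0.85 = 141, or 120 x 1.15 = 138.
- Design effect 1 + (6 - 1) x 0.04 = 1.20: 120 x 1.20 = 144. This is close, but a design effect raises the number required, not the number collected.
- Counting waves: 240 for two, 360 for three.
- A looser reading of about 20 does not help. With "an average cluster size of 15 patients", 240 patients come from 240/15 = 16 units, which is 16 x 6 = 96 records.

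**3. Can 146 be reproduced as a power result?** Not without a standard deviation (SD). Solved backwards with z(0.975) + z(0.80) = 2.80 and design effect 1.20:
- Two-sample comparison, 73 per arm: SD = 3 x sqrt((73/1.20)/2)/2.80 = about 5.9.
- Paired, 146 in one sample: SD of differences = 3 x sqrt(146/1.20)/2.80 = about 11.8.
- Paired, 73 per arm: 3 x sqrt(73/1.20)/2.80 = about 8.4.

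The article gives nothing to choose between these, so 146 is neither confirmed nor refuted as a requirement.

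**4. Power with 120 records, taking 146 as 80%.** With cluster size unchanged at 6, the SD and the design effect cancel: power = Phi(2.80 x sqrt(n/146) - 1.96).
- n = 120: Phi(2.80 x 0.907 - 1.96) = Phi(0.58) = 0.72.
- n = 96 (16 units): 0.62.
- If 146 already includes 15% attrition (assumption), the net need is 146 x 0.85 = 124.1, and 120 analysable records give Phi(2.80 x sqrt(120/124.1) - 1.96) = 0.79. This also needs the records of departed patients to be replaced.
- If the correlation of 0.04 holds across the 12 records of a home (assumption), the design effect is 1 + 11 x 0.04 = 1.44. Power is then Phi(2.80 x sqrt((120/1.44)/(146/1.20)) - 1.96) = 0.64.

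**5. Would eight records per unit settle it?** This gives 8 x 20 = 160 records.
- Clustering by unit: design effect 1 + 7 x 0.04 = 1.28, effective number 160/1.28 = 125 against 146/1.20 = 121.7, power about 0.81.
- Clustering by home: design effect 1 + 15 x 0.04 = 1.60, effective number 100, power about 0.72.

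So no number per unit can be fixed until the clustering level is settled.

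**The case against.** The strongest reply is that N-Catch is one of two measures of change in care, that this is a secondary outcome, and that the article cites Figure 1 beside the calculation, which is not available in the text at hand. All of that is true and limits the weight of the point. It does not remove the conflict, because the text alone gives incompatible numbers.

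It can also be said that sizing a study with a simpler test than the final model is common. That stands. A reader might infer that the paired t-test is a before-after comparison within patients, so that the stated power belongs to a different question. The article does not establish this: it never says what is paired, and under Randomization and allocation homes are put in pairs by size, so a matched between-arm reading is possible. What remains is that the basis is unclear and does not match the planned analysis.

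A reader might also take 64% as the true power. It rests on an assumed home-level correlation. The article gives none, and the correlation evidence it names concerns fecal incontinence, not N-Catch.

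On selection, a reader might infer that intervention staff pick the audited records at baseline and that the first six names are redrawn at each wave. Baseline data are collected before allocation, so staff in both future arms work under the same rule with the same knowledge. The article states the rule once and does not say whether patients are followed or redrawn. Selective documentation is therefore a possible bias, not one that the documents show. The Discussion already discloses that the data collectors are unblinded.

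**Conclusion.** The stated requirement and the planned yield contradict each other: 120 records against 146, a shortfall of 18% that attrition, repeated waves or a looser count of units does not explain. If 146 records are taken as the stated 80% power, 120 give about 72%. The range is about 79% if an unstated 15% attrition allowance is already included, down to about 64% if the correlation of 0.04 is assumed to hold within homes. These figures show the relative loss. They do not validate 146, which cannot be checked without the SD. The mismatch between the paired t-test and the mixed model is a reason to recompute, not proof that the calculation answers the wrong question. The predictable selection of records is a secondary weakness. The primary outcome and its analysis are not affected.

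**What to change.** Recompute the record requirement for the between-arm comparison in the planned mixed effects model. State the SD, the level of clustering (unit, home or both), any attrition allowance, and whether the same patients are followed. Then make the figures agree, either by restating the power that 120 records deliver or by raising the records per unit to the recomputed number. The 72% above should not be printed as the result, since it inherits the calculation that needs replacing. The cost is a corrected figure, or a few more records per unit.

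To make selection less predictable, the blinded research assistant could draw records at random from the coded patient list and disclose the draw only at extraction. If records are redrawn at follow-up, some within-patient pairing is lost, and with it some precision for a change outcome. The recomputed requirement should allow for that.
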